# STUDY DESIGN

This study will be a non-blinded, multicentre Randomized Controlled Trial (RCT), conducted in the ED of the MCL and other cooperating hospitals. Patients with a confirmed proximal- or neck of femur fracture are randomized to one of three treatment arms: FICB, FNB or PENG. After randomization regional anaesthesia is provided according to a standardized protocol and pain scores are measured at fixed time intervals. Patient reported outcomes are measured with a validated (QoR-15) questionnaire either 6-8 hours after block administration or before admittance to the operating room (OR), whichever one comes first. A flowchart of the study design can be found below (*Figure 1*).

**Figure 1**. Flowchart of the study design.

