## Sample size calculation

Sample size was based on the primary outcome measure (QoR-15 score) and a superiority design. Following this design, an independent samples t-test was used, reasoning that one block would be superior to all others if it outperforms its best performing competitor. Based on previous research, a clinically relevant difference is determined at 6.0 points difference in QoR-15 scores.^27^ Also based on previous literature, a standard deviation of 10 is used.^28-30^ A power of 0.9 is used to minimize the chance of missing differences between the groups, as the differences in scores are likely to be small. In order to detect this difference between any of the three groups with a pre-defined p-value of 0.05, 180 patients are needed (distributed over three groups of 60). To account for 10% attrition, i.e. potential dropouts during the study process, a total of 198 patients will be included.

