### Medication and dosage

As allocation to the treatment arms will be balanced for each participating centre, participating medical centres should use the NYSORA procedures for ultrasound guided nerve block placement.^31-33^ The type of LA (such as levobupivacaine or ropivacaine) used can be the one of their preference. While doing so, they have to adhere to the dosing recommendations in Table 1. In line with existing guidelines, high-volume low-concentration blocks are advised for FICB and PENG blocks specifically.

|  | **Levobupivacaine** | **Ropivacaine** |
| --- | --- | --- |
| Relative maximal allowed dosage | 2mg/kg | 3mg/kg |
| Absolute maximal allowed dosage | 200mg | 300mg |
| Advised dosage  Weight of 50-60kg  Weight of >60kg | 75mg  100mg | 112,5mg  150mg |

Table 1. Allowed and advised dosages of local anaesthetics.

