## Rescue medication (if applicable)

Cooperating medical centres can use their standard, already existing procedures for escape medication by means of opioids. To account for different opioids used in different centers, dose equivalents will be calculated for comparison.

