## Randomisation, blinding and treatment allocation

Block-randomization will be performed via the REDCap randomization module on a 1:1:1 basis for every participating centre.

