## Study procedures

Before the start of the data collection, a refamiliarization session for all three nerve block procedures will be hosted in each individual center. In this refamiliarization session, an expert in POCUS will provide theoretical and practical training in block placement for each of the three blocks, and will test and log the skill level of the participating physicians in a dedicated training log. Only physicians who are able to perform all three blocks in line with the NYSORA guidelines are eligible for participation in the study.^31-33^

[figure not shown]

**Figure 2**. Timeline of the study procedure, showing which data will be collected at what time point.

Data will be gathered at 6 different time points (T1-T6). *Figure 2* shows a detailed timeline of data collection.

Pre-block characteristics (demographic data (age, sex, weight), ASA score, pain scores (VAS) during rest and light elevation of the affected leg, type of fracture, analgesics administered before hospital admission (including medication routinely used by the patient), block characteristics (type of block, visualization of landmarks, amount- and type of LA administered, timing of block placement), and post-block characteristics (total amount of opioids administered in the first 12 hours after block administration and (S)AE’s) will be reported in an electronic case report form (appendix IV).

The primary endpoint, quality of recovery, will be measured either 6-8 hours post-block, or pre-OR (whichever one comes first) with the Quality of recovery-15 (QoR) patient-reported outcome questionnaire that measures the quality of recovery after surgery and anaesthesia.^34^ To ensure patients will be adequately rested for their operation, QoR-15 registration will be postponed until the next morning for blocks placed between 17.00 and 22.00 hours, as QoR-15 registration would then fall between 23.00 and 6.00. The QoR-15 questionnaire can be found in the appendices (*Appendix III*). Previous studies have shown a good convergent validity between the QoR-15 and the visual analog scale (VAS). Additionally, validity of the QoR-15 is supported by a negative correlation with duration of surgery and duration of hospital stay, and the QoR-15 shows excellent internal consistency, split-half reliability, test–retest reliability, and responsiveness.^34^

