# STATISTICAL ANALYSIS

Standard descriptive statistics will be used to summarize patient characteristics. Continuous data will be inspected for normality before analysis (Shapiro-Wilk), summarized with mean and standard deviation if normally distributed, or median and 25-75th centiles (Q1, Q3) if not normally distributed, and evaluated for differences with the One-Way ANOVA (if normally distributed) or Friedman Test (if not normally distributed). Categorical data will be summarized by frequency count and percentage calculations. Examination of possible associations between data will be done by Chi-Square Test or Logistic Regression. LA-type will be used as an interaction term to investigate the influence of the type of LA used. If needed, quantile regression, suitable for skewed data, will be used to identify confounders that may impact on postoperative quality of recovery scores. A two-tailed P-value <0.05 will be taken to indicate statistical significance.

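### Centres choose the local anaesthetic, so where a centre uses one agent the planned LA interaction cannot be credited to the drug

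*Protocol*

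**What the plan says.** The trial is multicentre, "conducted in the ED of the MCL and other cooperating hospitals". The number of centres is not given.

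On allocation, section 5.2 says: "Block-randomization will be performed via the REDCap randomization module on a 1:1:1 basis for every participating centre". The randomised factor is the block, balanced inside each centre.

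On the drug, section 4.1.2 addresses the centres ("As allocation to the treatment arms will be balanced for each participating centre, participating medical centres should use the NYSORA procedures") and continues: "The type of LA (such as levobupivacaine or ropivacaine) used can be the one of their preference". The choice of local anaesthetic (LA) is thus handed to centres and is not randomised. Section 4.2 gives centres a similar freedom over rescue: "Cooperating medical centres can use their standard, already existing procedures for escape medication by means of opioids".

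On recording, section 5.3 lists the data captured for each patient, including "block characteristics (type of block, visualization of landmarks, amount- and type of LA administered, timing of block placement". The case report form in Appendix IV also has a field for the agent and its dose.

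On analysis, section 7 compares continuous outcomes across the three blocks by one-way ANOVA, or a rank-based test if the data are not normal. It then adds: "LA-type will be used as an interaction term to investigate the influence of the type of LA used". It names no centre term, does not call the LA analysis exploratory, and closes with a general two-sided 0.05 threshold.

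**The concern.** If a centre uses its preferred agent throughout, LA type is a label for a group of centres. Those centres also differ in operators, case mix and, as section 4.2 expressly allows, rescue-opioid procedures. Any of these could make the difference between blocks larger in one group of centres than in the other. A block-by-LA interaction would pick that up and, under the purpose stated in section 7, it would be reported as something the drug did.

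The opposite result carries its own risk. The trial is sized for a contrast between two blocks. A test of whether that contrast differs between agents is much less precise, so a non-significant result says little about whether the agent matters.

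What is at stake is an ancillary conclusion about LA type. The main comparison of the three blocks is not in question.

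**Working it through.** **Inputs from the protocol.** Section 3.4: difference of interest 6.0 points ("a clinically relevant difference is determined at 6.0 points difference in QoR-15 scores"), SD 10, power 0.9, significance level 0.05, 60 per arm, 180 in total, 198 after 10% attrition. Section 7: two-sided testing. **Not in the protocol, so assumed:** the number of centres, the agent each one uses, the split of patients between agents (two agents are taken here), and the variation between centres.

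**1. The plan's own figure.** A two-sample t-test with difference 6, SD 10 and two-sided 0.05 reaches power 0.898 at 59 per arm and 0.903 at 60 per arm. So 60 × 3 = 180 is reproduced, and 180 × 1.10 = 198. The standard error of a block contrast is 10 × √(2/60) = 1.83.

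**2. What can be separated.** If each centre uses one agent, the LA indicator is the sum of the indicators of the centres using that agent. The block-by-LA columns are then sums of block-by-centre columns. Rank checks of the design matrix, identical for 2, 4 and 6 centres, give these added degrees of freedom:

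| Term added | One agent per centre | Agents mixed within centre |
|---|---|---|
| LA, given centre and block | 0 | 1 |
| Block-by-LA, given centre, block and LA | 2 | 2 |
| Block-by-LA, given block-by-centre as well | 0 | 2 |

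With one agent per centre the interaction can be estimated, because every centre contains all three blocks. It is, however, fully aliased with block-by-centre variation.

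**3. What that does to the test.** This was a simulation of 180 patients in equal centres, one agent per centre, no true LA effect, an assumed SD of 3 points between centres, and 2,000 runs per setting. It gives the proportion of trials with a significant block-by-LA test. Where two figures appear, the first is without and the second with centre main effects in the model.

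| Centres | Centre-by-block SD 0 | SD 2 | SD 3 |
|---|---|---|---|
| 2 | 5.6% | 28.8% | 47.6% |
| 4 | 4.0% / 4.8% | 13.5% / 14.6% | 23.9% / 25.7% |
| 6 | 3.8% / 4.6% | 8.8% / 10.6% | 16.3% / 18.8% |

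The test holds its level if block differences are the same in every centre, and does not if they vary. Adding centre as a main effect does not cure this.

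**4. Power, leaving confounding aside.** Let n1 and n2 be the patients per arm on each agent, with n1 + n2 = 60. The standard error of the difference between two block contrasts is 10 × √(2/n1 + 2/n2).

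- 50:50 (30 and 30): SE = 10 × √(2/30 + 2/30) = 3.65, twice the 1.83 above. Power at 6 points = Φ(6/3.65 − 1.973) = Φ(−0.33) ≈ 37%.
- 80:20 (48 and 12): SE = 10 × √(2/48 + 2/12) = 4.56. Power = Φ(6/4.56 − 1.973) = Φ(−0.66) ≈ 26%.

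The interaction detectable with 80% power is (1.960 + 0.842) × SE, which is 10.2 points at 50:50 and 12.8 at 80:20. The protocol sets no target for an interaction. The 6 points are borrowed from the block comparison as a yardstick.

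**The case against.** The strongest reply is that nothing in the protocol obliges a centre to keep to one agent, and the agent is recorded for each patient. A reader might infer from section 4.1.2 that LA and centre are inseparable and that no model could part them. The text does not support that. It suggests one agent per centre without requiring it, and with mixed use the terms can be separated, as the table shows. Even with single-agent centres the interaction is estimable and keeps its error rate when block differences do not vary by centre. This part stands, and the point is conditional for that reason. It does not rescue a drug reading: a choice of agent that varies within a centre is still not randomised.

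A reader might also infer that the LA term weakens the primary comparison. Section 7 does not support that either. The test it names for group differences is a one-way ANOVA, which has no place for an LA term, so the interaction must belong to another model.

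A third tempting reading is that an interaction term is the wrong quantity altogether. The sentence can fairly be taken to mean the agent's influence on the differences between blocks, and that is what the term tests.

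Finally, LA type is in neither the objectives nor the endpoints, low power for a subsidiary interaction is common, and model details are often left to a statistical analysis plan, which was not available here. All true. But the protocol itself fixes the purpose of the analysis, and that purpose goes beyond what a centre-chosen agent allows.

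**Conclusion.** The point holds in conditional form. LA type is a non-randomised choice given to centres, and the planned interaction has no centre term. To the extent that centres use a single agent, the result cannot be told apart from block differences that vary by centre, and it should not be presented as the effect of the agent. How much this matters depends on facts the protocol does not give: how many centres take part, whether they mix agents, and whether block differences vary between them. Under the assumed settings the false-positive rate runs from the nominal 5% or so to nearly half of trials, the worst case being two centres with marked variation.

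The limit on reassurance does not depend on confounding. Power for a 6-point interaction is about 37% at an assumed 50:50 split and 26% at 80:20. The primary block comparison and the sample size are untouched.

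**What to change.** In section 7, replace the sentence on LA type with text to this effect:

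> The comparison of the three blocks is made without an LA term. Block differences will also be reported by LA type as estimates with 95% confidence intervals. Any test of block by LA type will be done in a separate model that includes centre. These analyses are exploratory and non-randomised, and neither a significant nor a non-significant result will be attributed to the LA itself.

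The last clause carries most of the weight, since a centre term alone does not remove block-by-centre variation. A cross-table of agent by centre, from data already collected, would show readers how far the two coincide.

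The cost is one sentence. Data collection, sample size and treatment stay as they are. The small downside is that the trial gives up a confirmatory statement about LA type, which its design does not support.

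### Arms are balanced within centre and pre-block pain is collected, but the named tests use neither; covariates enter only through an optional confounder search on a mis-timed score

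*Protocol*

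**What the plan says.** Protocol section 5.2 sets the allocation: "Block-randomization will be performed via the REDCap randomization module on a 1:1:1 basis for every participating centre". Section 4.1.2 (Medication and dosage) relies on this design ("As allocation to the treatment arms will be balanced for each participating centre") when it lets each centre use the LA it prefers.

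Section 5.3 lists the pre-block data, among them "pain scores (VAS) during rest and light elevation of the affected leg", together with age, ASA score and fracture type.

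Section 7 (Statistical Analysis) compares continuous data by one-way ANOVA if a Shapiro-Wilk check supports normality, and by a Friedman test if it does not. Neither is given a covariate or a centre term. LA type is the only model term named, as an interaction. Other covariates come in only if needed: "quantile regression, suitable for skewed data, will be used to identify confounders that may impact on postoperative quality of recovery scores". The significance rule is "A two-tailed P-value <0.05 will be taken to indicate statistical significance".

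Sections 2 and 5.3 place the QoR-15 at 6-8 hours after the block or before surgery, whichever is first. For blocks placed between 17.00 and 22.00 it moves to the next morning, so that patients are rested for their operation.

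**The concern.** There are three linked problems, all in text that section 7 does state rather than leave open.

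1. **The stratum is not in the test.** When arms are balanced within centre, differences between centres cancel from the arm contrast. A one-way ANOVA still leaves that variance in its error term, so its standard errors are too wide whenever centres differ. Pre-block pain, already collected, could also reduce the error term and is not used.
2. **Covariates are to be found rather than fixed.** Section 7 gives no trigger for the search, no candidate list and no rule for using what it finds. In a randomised trial baseline imbalance is due to chance, and covariates serve precision. Choosing them from the outcome data allows more than one adjusted result. That matters more in a non-blinded trial with a patient-reported primary endpoint.
3. **The target is mis-timed.** The search refers to postoperative scores, whereas the QoR-15 is meant to be completed before the operation.

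At stake are efficiency, a test that runs somewhat below its nominal level, and the clarity of any adjusted result. The validity of the randomised comparison is not at stake.

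**Working it through.** **Inputs from the protocol.** Section 3.4: "a clinically relevant difference is determined at 6.0 points difference in QoR-15 scores"; "a standard deviation of 10 is used"; "A power of 0.9 is used to minimize the chance of missing differences between the groups"; an independent-samples t-test; 60 per arm, 180 in total. Section 7: two-sided 0.05.

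**Inputs not in the protocol (assumptions).** The share of QoR-15 variance lying between centres (ICC): 0, 0.05 and 0.10. The correlation r between pre-block covariates and QoR-15: 0.1 to 0.5.

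**Step 1: the plan's own figure.** Standardised difference 6/10 = 0.6. The two-sided t-test at 0.05 with power 0.90 needs 59.35, so 60 per arm and 180 in total. Power at 60 per arm is 0.903. The stated size is reproduced, with no covariate reduction built in.

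**Step 2: level of the unadjusted three-arm F test.** Under within-centre balance the between-arm mean square reflects only within-centre variance, 100 × (1 − ICC), while the error mean square is close to the total, 100. The F statistic is therefore shrunk by about (1 − ICC). In large samples the 5% critical value for two numerator degrees of freedom is −ln(0.05) = 2.996, and the tail probability is exp(−x). The actual level is then exp(−2.996/(1 − ICC)):

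| Assumed ICC | 2.996/(1 − ICC) | Level |
|---|---|---|
| 0 | 2.996 | 5.0% |
| 0.05 | 3.153 | 4.3% |
| 0.10 | 3.329 | 3.6% |

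A simulation (4,000 runs per setting, 180 patients, five equal centres, blocks of six, total SD 10) agrees in direction. The unadjusted ANOVA rejected in 4.7% of null runs with no centre or baseline effect, 3.7% with centre at 5% of variance, and 3.5% with centre and baseline at 10% each. The model with centre and baseline gave 4.7%, 4.3% and 5.1%. The Monte Carlo standard error is about sqrt(0.05 × 0.95/4000) = 0.3 percentage points.

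**Step 3: precision forgone.** Residual SD = 10 × sqrt(1 − r²); the adjusted comparison of 60 per arm is worth 60/(1 − r²) unadjusted patients per arm.

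| Assumed r | Residual SD | Pairwise power for 6 points | Equivalent n per arm |
|---|---|---|---|
| 0 | 10.00 | 0.903 | 60 |
| 0.1 | 9.95 | 0.906 | 60.6 |
| 0.2 | 9.80 | 0.914 | 62.5 |
| 0.3 | 9.54 | 0.927 | 65.9 |
| 0.5 | 8.66 | 0.964 | 80 |

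In the same simulation, with true means 0, 3 and 6, power of the overall F test unadjusted against adjusted was 0.84 against 0.85 (centre 5%, baseline 0% of variance) and 0.85 against 0.91 (10% each).

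**Step 4: timing.** The schedule in sections 2 and 5.3 puts the QoR-15 after the block and before surgery, and the next-morning deferral is also framed as protecting rest before the operation. No section schedules a QoR-15 after surgery. The adjective in section 7 therefore has no matching measurement.

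**The case against.** The strongest reply is that nothing here is invalid. An unadjusted comparison of randomised arms is unbiased, under within-centre blocking it errs on the conservative side, and the trial was sized for an unadjusted t-test that reaches 0.903 at 60 per arm. All of that stands. It is also fair that the detailed covariate set commonly belongs in a SAP, and that the gains rest on assumptions: at r of 0.1 to 0.2 power moves only to 0.906-0.914, and at ICC 0 the level is exactly nominal. This limits the point to an efficiency and clarity recommendation. It does not remove it, because section 7 itself names unadjusted tests, an open-ended search and the wrong time frame, and a SAP would have to depart from that text.

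The wording of section 7 also sets limits. It never calls the ANOVA the primary test. The sentence covers continuous data in general and depends on normality. The search is conditional, and nothing says that its result would replace the arm comparison.

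A reader might further infer that the LA-type interaction is confounded with centre unless a centre term is added, because centres choose the LA. The design does not support this. Each centre contributes its own arm contrast, from which that centre's main effect cancels; comparing those contrasts between LA types therefore carries no centre main effect. What can remain is arm-by-centre variation, which a centre main effect does not remove. If each centre uses a single LA, the LA main effect also cannot be estimated beside fixed centre effects. Nor is low power for this interaction a contradiction, since the protocol claims none.

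**Conclusion.** The point holds as a recommendation on efficiency and pre-specification, together with one plain wording error. The named tests leave out the randomisation stratum and a baseline value that is already collected. Covariates are left to an undefined search, aimed at a postoperative score that the trial does not measure.

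Its size is modest: a level of about 4.3% to 3.6% for the three-arm F test at assumed ICCs of 0.05 to 0.10, and pairwise power of about 0.91 to 0.96 instead of 0.90 at assumed correlations of 0.2 to 0.5. The protocol supplies neither the ICC nor the correlation.

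A reader might infer a biased result or too small a sample. Neither follows: the comparison is unbiased and the sample size is reproduced.

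**What to change.** Changes to section 7:

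- State the QoR-15 comparison as a linear model on arm with centre and pre-block VAS, naming which pre-block VAS (rest or leg elevation) is used. Age, ASA score or fracture type may be added if fixed in advance.
- Adjust each post-block pain comparison for the matching pre-block VAS, rest with rest and elevation with elevation.
- Delete the search for confounders, or label it exploratory and state that it does not alter the arm comparison.
- Replace the postoperative label with the actual time point: after the block and before surgery.
- Label the LA-type interaction exploratory. No centre term is needed on the ground of removing confounding from it.

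The cost is a rewritten paragraph. The sample size does not change, and the covariates are already listed for collection in section 5.3. The readable text of the case report form in Appendix IV shows only post-block pain fields, but figures are missing there, so this is not an error; the sponsor need only confirm that the pre-block VAS field exists.
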